## Methods

### Participants

Participants in the current study will comprise Hong Kong Chinese older adults. Participants will be eligible if they are 65 years or over; retired or homemakers; willing to be randomly assigned to experimental or control groups; able to understand the study rationale; a first-language Cantonese-speaker; and, most importantly, non-vaccinated within 1 year and report never or rarely adopting any of the influenza prevention behaviors listed by the research group. Participants who report more frequent preventive behaviors will not be invited to attend the preliminary session. We will also exclude older adults who are dementia as well as who are fragile to move.

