### Phase 2 – implementation of the intervention

#### Sample size

We will assume a small effect size (Cohen’s *d* = .20) for the effect of the intervention in order to calculate a conservative post-intervention sample size sufficient to detect an effect. G*Power analysis using the between-factor (i.e., 3 groups) repeated measures (i.e., 4 phases; baseline, 3-month, 6-month, and 12-month measurements) multivariate analysis of variance (MANOVA) indicates that a sample size of 65 in each group is required at follow-up in order to detect a small effect size (*d* = .20) in the outcome variables with power (beta) set at .90 and significance level (alpha) set at .017 (i.e., .05/3). Based on conservative estimate of 25% attrition rates, we aim to recruit 261 participants at baseline (*n* = 87 participants per group).

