#### Data analysis

Data will be stored in password-protected spreadsheets saved on a computer of a member of the research team. Data will be initially treated for missing values with multiple imputation. The distribution of the data will be examined that the skewed data will be log-transformed and replaced with median (interquartile range). All analyses will be conducted using full intention-to-treat analyses with scores on dependent variables for non-compliers carried over using the last-observation carried forward method. Independent samples t-tests and chi-square analysis will be used to test whether there are significant differences between non-compliers and compliers. We will analyze the effectiveness of the intervention using a series of linear mixed models on each behavioral and psychological outcome variable. In the analyses, four phases will be the within-participants factor and three intervention conditions will be the between-participants factor. Baseline scores for the dependent variables will be included as covariates in the analysis with salient demographic variables: age, gender, marital status, education level, and socioeconomic status. We will use Akaike and Bayesian information criteria to assess whether a compound symmetry covariance structure will provide the best model fit of each outcome variable. The phase (i.e., time of measurement) by intervention condition (i.e., behavior initiation + behavior maintenance; behavior initiation only; and control group) interaction will be the central test. Beyond main effects of the intervention, we will also test whether there are any statistically significant interactions between the intervention condition and the time factor. For all tests, the Cohen’s d effect size will be calculated associated with a 95% confidence interval. Structural equation modelling (SEM) will be used to test the hypothesized theoretical sequence in the HAPA model [25]. In the analyses, the effect of the intervention group conditions will be included using a dummy coded variable along with the demographic and baseline variables. The 95% bias corrected (BC) bootstrapping method (with *n* = 5000 bootstrap resamples) was subsequently employed to test the indirect effects of mediators (e.g., intention, maintenance and recovery self-efficacy, action and coping planning) (25). The CONSORT Extension for Nonpharmacological Treatment Interventions will be followed to report the results.

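### Compound symmetry is kept or dropped for each outcome from the trial data on AIC and BIC with no precedence; under moderate departures, visit-specific and pairwise contrasts can be miscalibrated by about 1 to 3 points

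*Protocol article*

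**What the plan says.** The Data analysis section plans "a series of linear mixed models on each behavioral and psychological outcome variable", in which "four phases will be the within-participants factor and three intervention conditions will be the between-participants factor". It adds that "Baseline scores for the dependent variables will be included as covariates in the analysis". The covariance rule, applied outcome by outcome, is to "use Akaike and Bayesian information criteria to assess whether a compound symmetry covariance structure will provide the best model fit". No competing structure is named, and nothing says which criterion prevails if they conflict.

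The phase-by-condition "interaction will be the central test", and every test is to carry a Cohen's d with a 95% interval. The Sample size section gives the visits as "4 phases; baseline, 3-month, 6-month, and 12-month measurements", with 65 participants per group at follow-up. No visit-specific SDs or between-visit correlations are given.

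**The concern.** Compound symmetry assumes the same variance at every phase and the same correlation between any two visits, whether 3 or 12 months apart. Unequally spaced visits over a year make fading correlation a reasonable expectation. For the behaviours, eligibility gives a second reason for doubt: entrants must "report never or rarely adopting any of the influenza prevention behaviors listed by the research group", which should compress the spread at baseline. Carrying observations forward for non-compliers also ties later values together.

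The standard errors of the phase-specific contrasts depend on the structure retained. Under the stated rule that structure is settled after the data are seen, separately for each outcome. When the criteria point different ways, the choice is left to the analyst. After multiple imputation the criteria may also differ between completed datasets.

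**Working it through.** **Inputs from the protocol article.** Three groups of 65 at follow-up, so n = 195; 65/0.75 = 86.7, rounded up to 87 per group and 261 recruited, as stated. Four phases. Baseline also enters as a covariate, so both a four-phase model and a three-visit model conditional on baseline are checked.

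**Assumed.** The alternative structure is unstructured, data are complete, and all covariance scenarios below are illustrative.

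**Thresholds.** With m visits, unstructured has m(m+1)/2 parameters and compound symmetry has 2. Unstructured wins when the likelihood-ratio statistic exceeds 2Δ (AIC) or Δ·ln n (BIC).
- Four phases: Δ = 10 − 2 = 8. AIC 16; BIC 8 × ln 195 = 8 × 5.273 = 42.2.
- Three visits: Δ = 6 − 2 = 4. AIC 8; BIC 4 × 5.273 = 21.1.

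The criteria disagree only when the statistic lies between the two values.

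**How often they disagree (calculated and simulated at 65 per arm).**

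| True covariance | Four phases | Three visits |
|---|---|---|
| Compound symmetry true | 5% | 10% |
| Variance +10% per visit | 30% | 24% |
| Mild correlation decay, .60 to .45 | 57% | 47% |
| Variance +25% per visit | 80% | 57% |
| Strong serial decay, 3-month correlation .6 to .9 | 0–1% | 0–6% |

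**Worked scenario: equal SDs, fading correlation.** Correlations with baseline are .59, .50 and .40 at months 3, 6 and 12; month 3 with 6 is .59, 3 with 12 is .44, 6 with 12 is .50. The mean is 3.02/6 = .503. In simulation AIC keeps compound symmetry in about 20% of trials and BIC in about 97%; they disagree in 76%.

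*Change contrasts, four-phase model.* The variance of a change is 2(1 − r); compound symmetry uses 2(1 − .503) = 0.993 for every pair.
- Month 12 minus baseline: true 2(1 − .40) = 1.20. SE ratio √(0.993/1.20) = 0.910; 1.96 × 0.910 = 1.783; two-sided rejection 7.5%. Simulations gave 7.0–7.2%.
- Month 3 minus baseline: true 2(1 − .59) = 0.82. SE ratio √(0.993/0.82) = 1.101; 1.96 × 1.101 = 2.157; rejection 3.1%. Simulations gave 3.2–3.6%.
- Letting BIC choose gave 7.0% and 3.4%; unstructured gave 4.7–5.3%.

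*Visit contrasts, conditional on baseline.* Residual variance is 1 − r²: 0.652, 0.750 and 0.840 at months 3, 6 and 12, mean 0.747.
- Month 12: √(0.747/0.840) = 0.943; 1.96 × 0.943 = 1.849; rejection 6.5%.
- Month 3: √(0.747/0.652) = 1.071; 1.96 × 1.071 = 2.099; rejection 3.6%.

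The direction therefore does not need rising raw variance; fading correlation with baseline is enough.

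**Other patterns.**
- Baseline SD 0.8, later SDs 1, all correlations .5. The true variance of the 12-minus-baseline change is 0.64 + 1 − 0.80 = 0.84. Compound symmetry uses mean variance (0.64 + 3)/4 = 0.91 and mean covariance (3 × 0.40 + 3 × 0.50)/6 = 0.45, hence 2(0.91 − 0.45) = 0.92. SE ratio √(0.92/0.84) = 1.047; rejection about 4%, so the test is now conservative. The criteria disagreed in 84% of simulated trials.
- Variance rising 1, 1.25, 1.5, 1.75, compound symmetry used: coverage 96.0% at month 3 and 92.0% at month 12 (95.7% and 92.5% after BIC selection).
- Variance falling by the same steps: 93.9% and 97.7%, the reverse.
- Unstructured fixed in advance: 94.7–95.3% at every visit in every scenario. AIC selection stayed within 94.5–95.6%.

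**Omnibus test.** With compound symmetry forced in the worked scenario, the phase-by-condition test rejected in 5.0–5.5% at the .05 level, and in 5.6% conditional on baseline. At .017 the figures were 1.8% and 2.1%.

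**The case against.** Information-criterion checks of compound symmetry are common and disclosed, and they do not assume that it holds. Candidate structures, tie-breaks, degrees of freedom and convergence fallbacks are often left to an analysis plan, which is not shown. That stands: their absence alone is no finding. What remains is the rule the article does state, a data-driven choice per outcome on two criteria with unlike penalties.

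Three stronger readings are tempting and do not hold.
- A reader might infer that AIC and BIC usually disagree at this sample size. The documents do not say so, and it is not a property of n = 195. Disagreement is low when compound symmetry is true and also when it is badly wrong, because both criteria then reject it; it exceeds half only in a middle band.
- A reader might infer that the central test is compromised. It stays near nominal in these scenarios. Inflation to 6.6–7.8% appeared only under strong serial decay, where both criteria discard compound symmetry almost always.
- A reader might infer that month-12 intervals must be too narrow and month-3 intervals too wide. That is one plausible pattern. With equal variances in the four-phase model, group differences at single visits are correctly sized, and other variance patterns reverse the direction. The eligibility rule bears on baseline spread of the behaviours only; it says nothing about the psychological outcomes or the spread among later visits.

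**Conclusion.** The point holds in a limited form. The stated rule leaves a choice to be made after seeing the data. Where departure from compound symmetry is moderate and BIC decides, visit-specific and pairwise contrasts and their 95% intervals are miscalibrated by about 1 to 3 percentage points. The direction depends on a covariance pattern that the document does not give; all scenarios are assumptions, with complete data and an unstructured alternative. The effect is modest. It is still worth correcting, because the hypotheses compare the arms pairwise, the sustainability objective depends on later visits, the choice recurs for every outcome, and a better-calibrated method costs almost nothing.

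**What to change.** Replace the covariance sentence with: all linear mixed models use an unstructured within-participant covariance, fitted by REML with Kenward–Roger degrees of freedom; if a model does not converge, one named fallback applies (for example heterogeneous Toeplitz with robust standard errors); the structure is not selected by AIC or BIC.

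The change is to wording only. It adds eight covariance parameters with four phases (10 against 2) or four with three post-baseline visits (6 against 2), easily estimated from 195 to 261 participants. If compound symmetry is true, the loss of precision is negligible.

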### Amis of the current study

In order to increase influenza prevention behaviors in Hong Kong older adults (aged 65 years and over), the aim of this project is to develop, implement, and evaluate a HAPA-based intervention, which comprises two main components of a health behavior change, namely, behavior initiation and behavior maintenance. Four specific objectives will be tested: (a) design and develop an intervention to promote influenza prevention behaviors consistent with guidelines of Department of Health in non-intending older adults; (b) imply the intervention in a sample of older adults in Hong Kong who reported never or rarely adopt influenza preventive measures during the past year using a randomized controlled trial; (c) evaluate the effectiveness and a 6-month sustainability of the intervention to change primary outcome variables (i.e., washing hands, avoid touching eyes, nose or mouth, facemask wearing, and vaccination); and (d) identify the psychological variables (i.e., intention, action and coping planning, maintenance and recovery self-efficacy) responsible for explaining the effect of the intervention.

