Five hypotheses will be tested in this project: (a) participants in the two intervention groups (i.e., behavior initiation + behavior maintenance; behavior initiation only) will have significantly higher rates of influenza prevention behaviors relative to participants allocated to the control group; (b) participants in the “behavior initiation + behavior maintenance” intervention group will have significantly higher participation in influenza prevention behaviors relative to participants allocated to the “behavior initiation only” intervention group; (c) participants in the two intervention groups (i.e., behavior initiation + behavior maintenance; behavior initiation only) will report significantly greater action self-efficacy, outcome expectancy, risk perception, and intention than participants in the control group. Participants in the “behavior initiation + behavior maintenance” intervention group will report stronger action and coping planning, maintenance and recovery self-efficacy, and social support than participants in the “behavior initiation only” intervention group and the control group; (d) participants in the “behavior initiation + behavior maintenance” intervention group will report significantly greater action self-efficacy, outcome expectancy, risk perception, and intention, and stronger action and coping planning, maintenance and recovery self-efficacy, and social support than participants in the “behavior initiation only” intervention group; (e) consistent with the propositions of the health action process approach, intention, action and coping planning, maintenance and recovery self-efficacy will mediate the effect of the intervention condition on influenza prevention behaviors.

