#### Preliminary group-based education session

Interested participants will be invited to attend an initial session where they will be screened for eligibility and be provided with full details of the study and an information and consent form pack. Participants will also be invited to participate in a one-off group education session on the general information about types of influenza, peak influenza season, routes of influenza transmission, and influenza preventive behaviors. Participants will then be randomized into one of the three conditions: (a) “behavior initiation” and (b) “behavior initiation + behavior maintenance”, and (c) “control group”. Randomisation will be conducted by a research staff who is blind to the composition of the participants using the online randomisation tool. Participants will be blinded to the intervention allocation, while the part-time research assistants will be blinded to the research purpose.

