#### Baseline measures

Participants will be asked to complete baseline demographic and psychological measures with the assistance of student helpers. Participants will be required to complete a questionnaire comprising: (a) demographic and economic variables (age, gender, education level, marital status and living arrangement, household income); (b) psychological variables using validated self-report measures of risk perception, outcome expectancies, action and coping self-efficacies, action and coping planning, and intention, with Chinese versions of these measures have been validated and used in a previous study [23], while items of recovery and maintenance self-efficacy [24] will be translated and back-translated and validated into Chinese prior to the start of study; and (c) influenza prevention behavioral variables (i.e., washing hands, avoid touching eyes, nose or mouth, and facemask wearing) will also be provided. In terms of the hand washing behavior, two situation-specific questions will be asked including (a) return to home and/or elderly center after being out and (b) before touching food. In terms of the behaviors of avoid touching eyes, nose or mouth, we ask how many times that participants be aware of and successfully inhibiting themselves touching their eyes, nose or mouth before they have washed their hands, particularly after they have been touching other objects that might lead them to exposure risk (e.g., stair rails and bannisters, door handles, chairs and tables, safety rails on the MTR etc.). In terms of the facemask wearing behaviors, we ask participants their facemask wearing behaviors when (a) in direct contact with people, (b) in crowded places such as shopping malls and the MTR. Participants will be informed that they will receive telephone calls in three randomly-selected days in the following 9 days asking them to report whether they have conducted the three influenza prevention behaviors. Participants’ self-reported clinical influenza episodes as well as flu-like symptoms during the past 3 months will also be collected.

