#### Follow-up measures

At the 3-month (i.e., the middle time point of the intervention after the behavior initiation session), 6-month (post-intervention), and 12-month follow-up occasions, participants will receive the same set of psychological outcome measures administered at baseline. They will also be asked to report the three influenza prevention behaviors (i.e., washing hands, avoid touching eyes, nose or mouth, and facemask wearing) as well as whether they get vaccinated via telephone calls in three randomly-selected days in 9 days. Participants’ self-reported clinical influenza episodes as well as flu-like symptoms during the past 3 months will also be collected. Participants will be reminded of their follow-up visit by telephone in advance of their visit. In order to minimize attrition, in particular participants from the control group, a fixed amount of monetary reward will be provided to those who completed all assessments.

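### Objective (d) sets out to name the variables that produce the intervention effect, but the planned bootstrap test supports this only if no unmeasured mediator–behaviour confounding remains

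*Protocol article*

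**What the plan says.** The aims section of the Protocol article gives objective (d) as to "identify the psychological variables (i.e., intention, action and coping planning, maintenance and recovery self-efficacy) responsible for explaining the effect of the intervention". Hypothesis (e) in the same section says that these variables "will mediate the effect of the intervention condition on influenza prevention behaviors".

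The Data analysis section describes the test: an SEM of the theoretical sequence, with dummy-coded condition, demographic variables and baseline variables. In it the 95% bias-corrected bootstrap with 5000 resamples is "subsequently employed to test the indirect effects of mediators".

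Three design facts bear on this:

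- **Randomisation.** The Preliminary group-based education session section says: "Participants will then be randomized into one of the three conditions". Condition is allocated; the mediators are not.
- **Mediators.** The Baseline measures section specifies "psychological variables using validated self-report measures", and the same instruments are repeated at follow-up.
- **Behaviours.** Under Follow-up measures, participants are "asked to report the three influenza prevention behaviors" by telephone, on three randomly selected days out of nine.

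**The concern.** An indirect effect is the product of two paths. Randomisation protects the first, from condition to mediator. It does not protect the second, from mediator to behaviour, which is an observational association between two reports by the same person. A common cause of both reports that the covariates miss enters the product as if it were mediation. More resamples do not help, because the bootstrap addresses sampling error only.

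Such a common cause is plausible here. Weekly coaching calls can change engagement, or the wish to give a good account of oneself, after randomisation, and baseline covariates cannot capture that. The Process evaluation section treats planning questionnaires as evidence of compliance, while planning is also a hypothesised mediator. General engagement could thus raise both planning scores and reported behaviour. Eligibility requires that people rarely or never take preventive action, which narrows baseline behaviour and leaves it less able to carry information on response style.

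At stake is the mechanism conclusion: a variable that the sessions shift but that leaves behaviour unchanged could be credited with the effect. The Discussion plans to disseminate findings to policy and practitioner groups.

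**Working it through.** **The plan's own figures.** None is given for the mediation analysis. The sample size reproduces from its stated inputs: 65 / (1 − .25) = 86.7, rounded up to 87 per group, and 3 × 87 = 261. The follow-up size is therefore taken as 65 per arm, or 130 versus 65 if the two active arms are pooled.

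**Inputs.**
- From the Sample size section: d = .20, 65 per group at follow-up, 87 recruited per group.
- From Data analysis: a 95% bias-corrected bootstrap.
- Assumed, because the protocol does not give them: the residual mediator–behaviour correlation r (0 to .3) and the shift d that the sessions produce in a mediator (0 to .50, including .20).

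**Model.** With X = condition and independent standard normal errors e and u:

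M = d·X + e

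Y = .20·X + r·e + √(1 − r²)·u

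M has no effect on Y. Regressing Y on X and M nevertheless gives a coefficient of r on M, so the spurious indirect effect is d × r. At r = .1 / .2 / .3:
- d = .20: .02 / .04 / .06 SD, which is 10 / 20 / 30% of the assumed total effect of .20.
- d = .50: .05 / .10 / .15 SD, which is 25 / 50 / 75% of it.

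**How often the interval excludes zero although the true mediator effect is zero (%).**

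| Setting | d on mediator | r = 0 | r = .1 | r = .2 | r = .3 |
|---|---|---|---|---|---|
| 65 v 65, one mediator | 0 | 1 | 2 | 7 | 9 |
| 65 v 65, one mediator | .20 | 2 | 7 | 18 | 25 |
| 65 v 65, one mediator | .50 | 8 | 27 | 61 | 82 |
| 87 v 87, one mediator | .20 | 3 | 13 | 28 | 31 |
| 87 v 87, one mediator | .50 | 6 | 32 | 76 | 92 |
| 130 v 65, one mediator | .20 | 3 | 10 | 26 | 31 |
| 130 v 65, one mediator | .50 | 10 | 37 | 79 | 93 |
| 130 v 65, five mediators jointly | .20 | – | 9 | 12 | 16 |
| 130 v 65, five mediators jointly | .50 | – | 21 | 37 | 54 |

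The equal-arm rows use 1000 trials with 1000 resamples each. The 130 v 65 single-mediator rows use 600 trials with 600 resamples, and the joint rows 300 trials with 400 resamples. The largest Monte Carlo standard errors, √(.25/trials), are 1.6, 2.0 and 2.9 percentage points. A second 130 v 65 run at d = .20 gave 14 / 27 / 28% for r = .1 / .2 / .3. Raising r to .4 changes little at 65 per arm: 26% at d = .20 and 84% at d = .50.

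**What baseline adjustment removes.** A separate simulation let one shared response style drive mediator and behaviour, with the unique parts having a test–retest correlation of .5, and adjusted for both baselines. Raw shared correlations of .2 to .5 left these residual correlations:
- style fully stable over time: about .06 to .10;
- stability .8: .12 to .34;
- stability .6: .18 to .46.

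Stable confounding thus ends near the r = .1 column, while less stable confounding falls in the r = .2 to .3 columns or beyond.

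**The case against.** The case on the other side is substantial. No trial randomises its mediators, and the method chosen is conventional. A sensitivity analysis for confounding commonly sits in an analysis plan, which is not shown here, so its absence cannot be counted. Most of the wording is a test of theory, and the Abstract's Discussion speaks only of a potential mechanism. No passage says that a variable will be declared a mediator whenever its interval excludes zero. Response tendencies such as social desirability are plausibly stable, and the stated baseline adjustment would remove most of their influence. Questionnaires at the center and telephone reports on random days also differ in mode, which may weaken shared-method correlation. The planned SEM has several mediators, and joint modelling roughly halves many of the rates. The effectiveness analysis is not affected.

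Most of this limits the size of the problem. It does not answer the point about objective (d), which makes a causal claim without the hedge used in the Abstract and has a described test that cannot support that claim unconditionally. Baseline covariates do not reach confounding that arises after randomisation, and a difference in mode does not remove common causes.

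A reader might infer more: that variables with no effect on behaviour would often be declared mediators. The documents do not support that as a general statement. It needs both a variable that the sessions move and a residual correlation that survives adjustment, and the protocol gives a figure for neither.

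**Conclusion.** The point holds as a limit on what may be concluded. Objective (d) is worded more strongly than the planned analysis can bear; its conclusion is conditional on no unmeasured mediator–behaviour confounding after the covariates.

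For a variable that is moved but has no effect on behaviour, the single-mediator false-declaration rate is about 7–31% at d = .20 and r = .1 to .3. At d = .50 it runs from 27% at r = .1 to about 80–90% at r = .3. With five mediators modelled jointly it is 9–16% and 21–54% respectively. For a variable that the sessions do not move it is at most 9%, and with no residual correlation at most about 10%. Every r is an assumption, as is every d on a mediator: the protocol's d = .20 is a general figure, not one given for mediators. The percentages therefore show what could happen and do not forecast this trial. The first condition, that the sessions move these variables, is what hypotheses (c) and (d) predict.

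This is a cheap improvement to the mechanism claim, not a flaw in the test of effectiveness.

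**What to change.** 1. Reword objective (d) so that the analysis identifies variables 'consistent with mediating' the intervention effect.
2. State beside it, and beside hypothesis (e), that the conclusion assumes no unmeasured mediator–behaviour confounding after the demographic and baseline covariates.
3. For each indirect effect, report from the same SEM the residual mediator–behaviour correlation at which it becomes zero. In a single-mediator linear model this is the partial correlation of mediator and behaviour given condition and covariates. In the full model it comes from refitting with the residual correlation fixed at a series of values.

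Report that value for readers to weigh, without a pass/fail cut-off: nothing in the protocol justifies a particular threshold, and any single number would be arbitrary.

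The cost is a little extra analysis on data already planned and two reworded sentences, with no change to participants, measures or design. The downside is that the mechanism claim may turn out weaker.
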